|  | 
 
4) Subjects with clinically significant abnormalities in the neurological examination performed at the screening visit
 
5) Subjects with any of the following vital signs at the screening visit 
 
✓ Systolic blood pressure (SBP): < 90 mmHg or > 140 mmHg
 
✓ Diastolic blood pressure (DBP): < 50 mmHg or > 90 mmHg
 
✓ Heart rate: < 50 bpm or > 90 bpm
 
 
 
6) Subjects with any of the following clinical laboratory test results at the screening visit 
 
✓ AST, ALT: > upper normal limit × 1.5
 
✓ Total bilirubin: > upper normal limit × 1.5
 
✓ CPK: > upper normal limit × 1.5
 
✓ Creatinine clearance calculated by CKD-EPI equation: < 60 mL/min/1.73m^2
 
✓ Subjects with a positive result in the serology test (syphilis test, Hepatitis B surface antigen, Hepatitis C antibody, Human immunodeficiency virus(HIV) antibody)
 
 
 
7) Subjects with any of the following ECG results at the screening visit 
 
✓ PR > 210 msec
 
✓ QRS complex > 120 msec
 
✓ QTcB > 450 msec
 
✓ Other, clinically significant arrhythmias
 
 
 
8) Subjects with a history of hypersensitivities including drug allergies (caused by aspirin, antibiotics, etc.), or a history of clinically significant hypersensitivities
 
9) Subjects with a history of alcohol or drug abuse, or with positive reaction to any drug of concern for abuse/misuse at the urine drug screening test
 
10) Subjects who had taken or are expected to take any prescription drug or herbal medicine within 2 weeks or any over the counter (OTC) drug within 1 week prior to the first administration day (however, subjects fulfilling other conditions could participate in the study at the investigator's discretion)
 
11) Subjects who had taken an inducer or inhibitor of drug metabolism such as barbiturates etc. within 1 month prior to the first administration day
 
12) Subjects who had participated in another clinical study (including bioequivalence studies) within 6 months prior to the first administration day
 
13) Subjects who had donated whole blood or component blood, or received transfusion within 3 months prior to the first administration day
 
14) Subjects who drink continuously (more than 21 units/week, 1 unit = 10 g of pure alcohol) or are unable to stop drinking during the period from 3 days prior to the first administration day to the end of the study
 
15) Smokers (except for whom quitted smoking prior to the first administration day for at least 3 months) or who cannot stop smoking during the period from 3 months prior to the first administration day to the end of the study
 
16) Subjects who cannot stop taking grapefruit or food containing grapefruit during the period from 3 days prior to the first administration day to the end of the study
 
17) Subjects who have taken excessive amounts of caffeine (> 5 units/day) on a continuous basis or who cannot stop taking caffeine or food containing caffeine (coffee, tea(black tea, green tea, etc.), carbonated drink, coffee-flavored milk, nutritional tonics, etc.) during the period from 3 days prior to the first administration day to the end of the study
 
18) During the entire study period and for at least 3 months after the last administration of the investigational drug, subjects who are unable to use an appropriate, medically accepted double contraception method or medically acceptable contraceptive method for themselves or their spouse or partner and who do not agree not to donate sperm by that period. 
 
✗ Medically acceptable contraceptive methods 
 
✓ Use of an intrauterine device with a proven rate of pregnancy failure in the spouse (or partner)
 
✓ Simultaneous use of a barrier contraception (for male or female) and spermicide
 
✓ Surgery of the person himself or his spouse(or partner) (vasectomy, salpingectomy/ligation,
 
 
 
 
 
 |

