administration of the test substance to rats at a dose of 50-200 mg/kg daily for 2 weeks, there were no deaths. As a result of oral administration to rats at doses of 30, 50, 75 and 100 mg/kg once daily for 4 weeks, histopathological changes due to administration of the test substance were observed in the kidneys, bladder, testis, epididymis and lungs. Renal epithelial hyperplasia and inflammatory cells infiltration in the renal pelvis observed in the male and female dose groups of 75 mg/kg or more, germ cell degeneration/loss and seminiferous tubules atrophy observed in the male dose groups of 75 mg/kg or more, and vacuole/degeneration of outer medullary tubules and basophilic tubules observed in the female dose groups were judged to be adverse effects due to administration of the test substance. Proximal tubular hyaline granules in the kidney, basophilic tubules, testicular germ cell degeneration/loss, and alveolar macrophage aggregation in the lungs(females) were observed even after a 2-week recovery period. Accordingly, in repeated administrations of rats for 4 weeks, the NOAEL(No Observed Adverse Effect Level) was determined to be 50 mg/kg/day for males and 30 mg/kg for females. As a result of repeated oral administrations of 0, 25, 50 or 100 mg/kg/day for 2 weeks to Cynomolgus Monkey, a dying condition or mortality was observed in male and female dose groups of 100 mg/kg/day and in male dose group of 50 mg/kg/day, and a distal tubule/collecting duct dilatation and papillary duct epithelial cell hypertrophy related to the test substance were observed in male and female dose groups of 100 mg/kg/day. As a result of repeated oral administrations of KDS2010 in monkeys at doses of 0, 10, 20, and 40 mg/kg for 4 weeks and observation of recovery for 2 weeks, there were no adverse effects related to the test substance and the NOAEL was judged as 40 mg/kg for both males and females. As a result of the safety pharmacology test, no effect of the test substance was observed in the tests to evaluate the effects of central nervous system, respiratory system, and cardiovascular system, and the IC50 in the hERG assay was  $7.8 \pm 1.7 \mu\text{M}$ . As a result of the genetic toxicology, the reverse mutation test, the chromosomal aberration assay, and the micronucleus assay were all negative.

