Vital signs include systolic blood pressure, diastolic blood pressure, pulse rate, and body temperature (tympanic membrane). Blood pressure and pulse rate are measured after maintaining a seated position for more than 3 minutes without sudden changes in position.

7) 12-Lead ECG

In addition to the basic recording, the ventricular rate (beats/min), PR interval (msec), QRS (msec), QT/QTcB (msec) at which automatic analysis & recording is output are recorded.

8) Pregnancy test

For all women of childbearing potential except surgical infertility, urine hCG test is performed.

9) Clinical laboratory test

Clinical laboratory tests include the following lists.

|                             |                                                                                                                                                                                                                                                    |
|-----------------------------|----------------------------------------------------------------------------------------------------------------------------------------------------------------------------------------------------------------------------------------------------|
| Hematology test      | WBC with differential count (segmented neutrophil, eosinophil, basophil, lymphocyte, monocyte), RBC, hemoglobin, hematocrit, platelet                                                                                                              |
| Blood chemistry test | AST, ALT, ALP, $\gamma$ -GTP, LDH, CPK, glucose, total cholesterol, triglyceride, creatinine, BUN, uric acid, total bilirubin, total protein, albumin, sodium, potassium, calcium, chloride, phosphorus, eGFR (measured using the CKD-EPI formula) |
| Coagulation test     | PT (INR), aPTT                                                                                                                                                                                                                                     |
| Urine test           | dipstick (color, pH, specific gravity, albumin, bilirubin, glucose, urobilinogen, ketone, nitrite, occult blood, WBC) microscopy (RBC, WBC, squamous cell, others)                                                                                 |

10) Alcohol breathing test

11) Cotinine & Urine drug screening

Amphetamines, barbiturates, benzodiazepines, cannabinoids, cocaine, opiates, cotinine

12) Serology test

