#### 3) 12-lead ECG

In addition to the basic recording, the ventricular rate (beats/min), PR interval (msec), QRS (msec), QT/QTcB (msec) at which automatic analysis & recording is output are recorded.

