#### 12.1.2. Safety/Tolerability Analysis

All AEs are classified using the MedDRA (Medical Dictionary for Regulatory Activities). Summarize the number of subjects (occurrence rate) and the number of occurrences of adverse events/adverse drug reactions and serious adverse events/adverse drug reactions by dose group and treatment group. Vital signs, 12-lead ECGs, and clinical laboratory tests are presented as descriptive statistics (mean, standard deviation, median, minimum, maximum) for the values measured at each time point and the amount of change from the baseline by dose group for continuous variables. In addition, for test results classified as normal, not clinically significant abnormal (NCS), and clinically significant abnormal (CS), a shift table after administration compared to the baseline is presented. A separate list is presented when there is a change from a normal or a not clinically significant abnormal (NCS) to a clinically significant abnormal (CS). Neurological examination summarizes the frequency of clinically significant abnormalities at each time point, and descriptive statistics according to appropriate classification such as dose group.

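### Bazett QTcB is the only heart-rate-corrected QT the protocol names; naming Fridericia QTcF, derived from QT and rate already recorded, would remove most of a plausible rate artefact at almost no cost

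*Protocol*

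**What the plan says.** Section 10.7.1 (Screening test, 12-Lead ECG) lists the variables kept from each tracing: "the ventricular rate (beats/min), PR interval (msec), QRS (msec), QT/QTcB (msec) at which automatic analysis & recording is output are recorded". Section 10.7.3 (Post-Study Visit) repeats the list: "PR interval (msec), QRS (msec), QT/QTcB (msec) at which automatic analysis & recording is output are recorded". Uncorrected QT and ventricular rate are therefore kept beside QTcB. For the treatment period, section 10.7.2 gives ECG times and windows but no list of intervals.

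QTcB also appears in the eligibility criteria (synopsis and 9.2.2), where "QTcB > 450 msec" excludes a subject. No other rate correction is named in the protocol.

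For analysis, section 12.1.2 says: "12-lead ECGs, and clinical laboratory tests are presented as descriptive statistics". These cover the value at each time point and the change from baseline, by dose group, with shift tables for normal, NCS and CS classifications. It does not say which QT variable is meant.

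ECGs on full-profile dosing days (1d in all studies, both periods of the food-effect cohort, and 7d in the multiple-dose study) are taken pre-dose and at 1, 2, 4, 8 and 12 h. Each cohort has 6 active and 2 placebo subjects.

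**The concern.** A reader who follows the text as written takes the listed ECG outputs, computes change from baseline, and obtains a Bazett-corrected QT summary. The square-root correction is free of heart rate only if QT really varies with RR^(1/2). If the true exponent is lower, QTcB rises when heart rate rises and falls when it falls, although repolarisation has not changed.

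Heart rate has reasons to differ between the baseline and the later ECGs:

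- Outside the fed period, the baseline follows a fast of at least 10 hours (10.4.1). Food is barred only until 4 h after dosing on full-profile days (10.1), so the 8 h and 12 h ECGs can follow meals.
- In the fed period, the high-fat meal starts 30 minutes before dosing (10.1), while the pre-dose ECG may be taken up to 60 minutes before (10.7.2.2). That baseline can precede the meal while the 1 to 4 h ECGs follow it.
- Subjects must sit at 45 degrees or more, or stand, until 2 h after dosing (10.4.1, 10.8). No such rule is stated before dosing.

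A rate shift common to active and placebo subjects would show in the placebo arm, but 2 placebo subjects per cohort estimate it poorly. At stake is a mean QTc change of several milliseconds, in either direction, that belongs to the correction formula rather than to the drug.

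**Working it through.** The protocol states no expected heart-rate change and no QT margin or precision, so there is no planned figure to reproduce.

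**Inputs from the protocol.** QT, ventricular rate and QTcB are recorded (10.7.1, 10.7.3). The screening exclusion "Heart rate: < 50 bpm or > 90 bpm" admits resting rates of 50 to 90 bpm.

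**Assumptions, not in the documents.** Rate-free QTc (QTc0) of 400 ms, range 380 to 450 ms. True QT-RR exponent b = 1/3, range 0.25 to 0.50. Heart-rate change of 5 or 10 bpm.

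**Formula.** RR = 60/HR in seconds. If QT = QTc0 × RR^b, then QTcB = QT/RR^(1/2) = QTc0 × (HR/60)^(1/2 − b). With b = 1/3 the exponent on HR/60 is 1/6, and the spurious change is QTc0 × [(HR₁/60)^(1/6) − (HR₀/60)^(1/6)].

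**Base case, QTc0 = 400 ms, b = 1/3.**

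| Heart rate (bpm) | Change in QTcB (ms) |
|---|---|
| 60 to 65 | 400 × (65/60)^(1/6) − 400 = +5.4 |
| 60 to 70 | +10.4 |
| 70 to 75 | +4.7 |
| 70 to 80 | +9.2 |
| 60 to 55 | −5.8 |
| 60 to 50 | −12.0 |

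**Range over QTc0 380 to 450 ms and starting rates 50 to 80 bpm, b = 1/3.** The smallest values come from 380 ms at 80 bpm and the largest from 450 ms at 50 bpm. A rise of 5 bpm adds 4.0 to 7.0 ms and a rise of 10 bpm adds 7.9 to 13.5 ms. A fall of 5 bpm subtracts 4.3 to 7.6 ms and a fall of 10 bpm subtracts 8.8 to 15.9 ms, so falls have a slightly larger effect than rises.

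**Dependence on the exponent, and what QTcF leaves behind.** QTcF = QT/RR^(1/3) = QTc0 × (HR/60)^(1/3 − b). For 60 to 70 bpm at QTc0 = 400 ms, the spurious change is 400 × [(70/60)^(1/2 − b) − 1] for QTcB and 400 × [(70/60)^(1/3 − b) − 1] for QTcF:

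| True b | QTcB (ms) | QTcF (ms) |
|---|---|---|
| 0.25 | +15.7 | +5.2 |
| 0.30 | +12.5 | +2.1 |
| 1/3 | +10.4 | 0 |
| 0.38 | +7.5 | −2.9 |
| 0.42 | +5.0 | −5.3 |
| 0.50 | 0 | −10.1 |

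QTcF is the closer of the two when b is nearer to 1/3 than to 1/2, that is, below (1/3 + 1/2)/2 = 5/12, about 0.417. When b lies between 1/3 and 1/2 the two corrections err in opposite directions, so reporting both brackets the true change.

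**The case against.** The strongest reply is that section 12.1.2 names no QT correction, and that the choice of derived ECG variables is commonly left to the SAP, which is not at hand. QTcF can be derived at any time from stored QT and rate, so nothing is lost. This stands in part. It limits the point to an improvement, because the protocol does not forbid QTcF. It does not remove the point, because the only correction the protocol does name is the rate-dependent one, and the cohort reviews under 10.5 use safety data during the study.

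The size is also conditional. The documents give no heart-rate effect of the drug, no QT-RR exponent and no QTc level. The table shows that the advantage of QTcF reverses above an exponent of about 0.417. That stands, and is the reason to keep QTcB beside it.

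Four stronger readings are tempting and are not supported:

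- **QT is recorded and analysed only as QTcB.** Uncorrected QT and ventricular rate are in the same list, and 12.1.2 names no correction.
- **The drug has a hERG signal.** Section 5.1.3 says "the IC50 in the hERG assay was" 7.8 ± 1.7 µM, but the same sentence reports no effect in the cardiovascular safety pharmacology tests. No margin can be computed, because molecular weight and unbound human Cmax are not given.
- **A fed-versus-fasted QT comparison would be distorted.** The planned food-effect comparison in 14.2 is of Cmax and AUC. No such QT comparison is stated.
- **The escalation review would be misled.** Sections 10.5 and 10.6 rest on CTCAE-graded events and discussion and contain no QTc rule, so no route from a shift of a few milliseconds to an escalation decision is documented.

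**Conclusion.** The point holds as a modest, nearly free improvement. With b = 1/3, QTc0 of 380 to 450 ms and starting rates of 50 to 80 bpm, QTcB moves by about 4 to 7 ms per 5 bpm rise and 8 to 13.5 ms per 10 bpm rise with no true change, and by similar amounts downward for falls. At an exponent of 0.42 the 60 to 70 bpm artefact is 5.0 ms, and at 0.50 it is zero. Whether heart rate will shift by this much is not known from the documents. The meal and posture conditions make a shift plausible, and 2 placebo subjects per cohort give little protection. QTcF removes the artefact at an exponent of 1/3 and most of it nearby. The QTcB eligibility limit is a separate clinical rule and is not addressed here.

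**What to change.** In section 12.1.2, state that QTcF = QT/RR^(1/3), with RR = 60/ventricular rate, is derived at each ECG from the recorded QT and ventricular rate. Make change in QTcF from 1d pre-dose the main QT summary, using each period's own pre-dose value in the food-effect cohort, and report QTcB beside it as supportive. Include the QTcF summary in the safety data given to the SRC. Because 10.7.2 lists no intervals, add a cross-reference there so that the 10.7.1 variable list clearly applies to treatment-period ECGs.

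The cost is one derived variable, a sentence or two of text and one more row in the ECG tables. No extra ECG, reader or subject visit is needed.

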### 10.7.2. Admission and Pharmacokinetic Evaluation Period

#### 10.7.2.1. Single ascending dose study(30 mg, 60 mg, 240 mg, 480mg, 960 mg)

## 1) Physical examination

Physical examination is performed on 1d pre-dose (0h), 2d 0h, 3d 0h, 4d 0h, 5d 0h, and 7d 0h.

| Scheduled time point       | Time window |
|----------------------------|-------------|
| 1d 0h, 2d 0h, 3d 0h, 4d 0h | -60 min     |

## 2) Vital sign

Blood pressure, pulse rate, and body temperature(tympanic) are measured on 1d pre-dose (0h), 1, 2, 4, 8, 12h post-dose, 2d 0h, 3d 0h, 4d 0h, 5d 0h, 6d 0h, and 7d 0h.

| Scheduled time point       | Time window |
|----------------------------|-------------|
| 1d 0h, 2d 0h, 3d 0h, 4d 0h | -60 min     |
| 1d 1, 2, 4, 8, 12h         | ±30 min     |

## 3) 12-Lead ECG

Electrography is performed on 1d pre-dose(0h), 1, 2, 4, 8, 12h post-dose, 2d 0h, 3d 0h, 4d, 0h, 5d 0h and 7d 0h.

| Scheduled time point       | Time window |
|----------------------------|-------------|
| 1d 0h, 2d 0h, 3d 0h, 4d 0h | -60 min     |
| 1d 1, 2, 4h                | ±20 min     |
| 1d 8, 12h                  | ±30 min     |

## 4) Pregnancy test

For all women of childbearing potential except surgical infertility, urine hCG test is performed before - 1d randomization.

## 5) Clinical laboratory test

Clinical laboratory tests are performed on 1d pre-dose (0h), 2d 0h, 3d 0h, 4d 0h, 5d 0h, and 7d 0h.

| Scheduled time point       | Time window |
|----------------------------|-------------|
| 1d 0h, 2d 0h, 3d 0h, 4d 0h | -60 min     |

Clinical laboratory tests include the following lists.

|                             |                                                                                                                                                                                                                                                    |
|-----------------------------|----------------------------------------------------------------------------------------------------------------------------------------------------------------------------------------------------------------------------------------------------|
| Hematology test      | WBC with differential count (segmented neutrophil, eosinophil, basophil, lymphocyte, monocyte), RBC, hemoglobin, hematocrit, platelet                                                                                                              |
| Blood chemistry test | AST, ALT, ALP, $\gamma$ -GTP, LDH, CPK, glucose, total cholesterol, triglyceride, creatinine, BUN, uric acid, total bilirubin, total protein, albumin, sodium, potassium, calcium, chloride, phosphorus, eGFR (measured using the CKD-EPI formula) |
| Coagulation test     | PT (INR), aPTT                                                                                                                                                                                                                                     |
| Urine test           | dipstick (color, pH, specific gravity, albumin, bilirubin, glucose, urobilinogen, ketone, nitrite, occult blood, WBC) microscopy (RBC, WBC, squamous cell, others)                                                                                 |

## 6) Neurological examination

A brief neurological examination (Appendix 2) is performed on 1d pre-dose (0h), 4h, 12h post-dose, 4d 0h, and 7d 0h.

| Scheduled time point | Time window |
|----------------------|-------------|
| 1d 0h, 4d 0h         | -60 min     |
| 1d 4, 12h            | ±30 min     |

## 7) Blood samplings and urine collections for PK analysis

Blood samplings for PK analysis are performed on 1d 0h (pre-dose), 0.33, 0.75, 1, 2, 3, 4, 6, 8, 12, 24, 48, 72, 96, 120, 144h post-dose, and urine collections for PK analysis are performed on 1d 0h (pre-dose), 0 ~ 12h, 12 ~ 24h (2d 0h), 24 ~ 48h (3d 0h), 48 ~ 72h (4d 0h) post-dose.

| Scheduled time point for urine collections                  | Time window |
|-------------------------------------------------------------|-------------|
| 1d 0h                                                       | -60 min     |
| 1d 0~12h, 12~24h (2d 0h),
24~48h (3d 0h), 48~72h (4d 0h) | ±30 min     |

## 10.7.2.2. Single dose study (120 mg, Food effect study)

## 1) Physical examination

Physical examination is performed on phase 1/2 1d pre-dose(0h), 2d 0h, 3d 0h, 4d 0h, 5d 0h, and 7d 0h.

| Scheduled time point                 | Time window |
|--------------------------------------|-------------|
| phase 1/2 1d 0h, 2d 0h, 3d 0h, 4d 0h | -60 min     |

## 2) Vital sign

Blood pressure, pulse rate, and body temperature(tympanic) are measured on phase 1/2 1d pre-dose(0h), 1, 2, 4, 8, 12h post-dose, 2d 0h, 3d 0h, 4d 0h, 5d 0h, 6d 0h, and 7d 0h.

| Scheduled time point                 | Time window |
|--------------------------------------|-------------|
| phase 1/2 1d 0h, 2d 0h, 3d 0h, 4d 0h | -60 min     |
| phase 1/2 1d 1, 2, 4, 8, 12h         | ±30 min     |

## 3) 12-Lead ECG

Electrography is performed on phase 1/2 1d pre-dose(0h), 1, 2, 4, 8, 12h post-dose, 2d 0h, 3d 0h, 4d 0h, 5d 0h, and 7d 0h.

| Scheduled time point                 | Time window |
|--------------------------------------|-------------|
| phase 1/2 1d 0h, 2d 0h, 3d 0h, 4d 0h | -60 min     |
| phase 1/2 1d 1, 2, 4h                | ±20 min     |
| phase 1/2 1d 8, 12h                  | ±30 min     |

## 4) Pregnancy test

For all women of childbearing potential except surgical infertility, urine hCG test is performed before phase1 -1d randomization and phase2 -1d.

## 5) Clinical laboratory test

Clinical laboratory tests are performed on phase 1/2 1d pre-dose(0h), 2d 0h, 3d 0h, 4d 0h, 5d 0h, and 7d 0h.

| Scheduled time point                 | Time window |
|--------------------------------------|-------------|
| phase 1/2 1d 0h, 2d 0h, 3d 0h, 4d 0h | -60 min     |

Clinical laboratory tests include the following lists.

|                             |                                                                                                                                                                                                                                                    |
|-----------------------------|----------------------------------------------------------------------------------------------------------------------------------------------------------------------------------------------------------------------------------------------------|
| Hematology test      | WBC with differential count (segmented neutrophil, eosinophil, basophil, lymphocyte, monocyte), RBC, hemoglobin, hematocrit, platelet                                                                                                              |
| Blood chemistry test | AST, ALT, ALP, $\gamma$ -GTP, LDH, CPK, glucose, total cholesterol, triglyceride, creatinine, BUN, uric acid, total bilirubin, total protein, albumin, sodium, potassium, calcium, chloride, phosphorus, eGFR (measured using the CKD-EPI formula) |
| Coagulation test     | PT (INR), aPTT                                                                                                                                                                                                                                     |
| Urine test           | dipstick (color, pH, specific gravity, albumin, bilirubin, glucose, urobilinogen, ketone, nitrite, occult blood, WBC) microscopy (RBC, WBC, squamous cell, others)                                                                                 |

6) Neurological examination

A brief neurological examination (Appendix 2) is performed on phase 1/2 1d pre-dose(0h), 4h, 12h post-dose, 4d 0h, and 7d 0h.

| Scheduled time point   | Time window  |
|------------------------|--------------|
| phase 1/2 1d 0h, 4d 0h | -60 min      |
| phase 1/2 1d 4, 12h    | $\pm 30$ min |

8) Blood samplings and urine collections for PK analysis

Blood samplings for PK analysis are performed on phase 1/2 1d 0h (pre-dose), 0.33, 0.75, 1, 2, 3, 4, 6, 8, 12, 24, 48, 72, 96, 120, 144h post-dose, and urine collections for PK analysis are performed on phase 1/2 1d 0h (pre-dose), 0 ~ 12h, 12 ~ 24h (2d 0h), 24 ~ 48h (3d 0h), 48 ~ 72h (4d 0h) post-dose.

| Scheduled time point for urine collections                         | Time window  |
|--------------------------------------------------------------------|--------------|
| phase 1/2 1d 0h                                                    | -60 min      |
| phase 1/2 1d 0~12h, 12~24h (2d 0h), 24~48h (3d 0h), 48~72h (4d 0h) | $\pm 30$ min |

